## Reporting Period

Complaints and adverse events are collected on an ongoing basis from baseline visit.

All new complaints and AEs must be recorded until the last study visit.

New protocol related complaints and AEs (caused by any intervention required by the protocol) and updates on AEs with an ongoing or unknown outcome must be recorded until the last subject visit required by the protocol. Beyond this reporting period, any new unsolicited serious AE spontaneously reported to the sponsor by the investigator would however be collected and processed.

Within a study, all patients who were exposed to the SENSIMED Triggerfish^®^ - whether they completed the recording session or not - should enter the complaint and AE recording period as defined above.

If a subject is documented as lost-to follow-up, ongoing/unknown outcome AEs will not be followed-up.

All ongoing/unknown outcome AEs will be followed-up until the last study visit. A last batch of queries will be sent after last study visit if remaining ongoing/unknown outcomes of reported AEs are pending.

After the last batch of queries with all collected data have been fully processed, CRFs and the database will no longer be updated. Only SAEs and medically relevant ongoing/unknown outcome AEs will be followed-up until resolution or stabilization or until 30 days after the subject was last exposed to the investigational device, whichever comes first.

# Statistical section

## Study Objectives

The objectives of this study are to assess the safety and effectiveness of the SENSIMED Triggerfish^®^ (TF) device in continuous recording of relative fluctuation in intraocular pressure (IOP). Safety will be assessed by recording of AEs during the 24 hours of continuous TF monitoring. TF efficacy will be evaluated by demonstrating TF ability to detect:

1. The known phenomenon of increase in IOP when moving from waking state to going to bed, as reflected in pneumotonometer measurements
2. Ocular Pulse frequency relative to direct measurement of Heart Rate (HR).

## Study Design

This is a single-center, single arm, open label study with subjects serving as their own control.

- Subjects will be monitored in a sleep laboratory with TF over 24 hours. All subjects will arrive at a similar time of day.
- Three (3) times during sleep HR will be measured directly over periods of six (6) minutes each. This duration has been chosen since TF activates every five (5) minutes for a single minute, and time of activation cannot be known until device recordings are examined. Thus the interval specified will ensure at least one, continuous thirty-second TF recording in parallel to HR measurement. Time of HR measurement will be logged and synchronized along with TF recording so that the two outputs can be compared at the same time points.
- Each subject will complete a diary of activities during the study. Of particular importance is the time at which subject went to bed at night.

## Population

Study population will consist of males and females whose inclusion and exclusion criteria are described in section 6.1.

## Overview of Investigation

Study procedures described in Section ‎1.2 are designed to evaluate TF's ability to:

- Detect changes in IOP from waking to sleep, based on the established phenomenon that IOP increases from waking to sleep hours.
- Accurately record the Ocular Pulse, which varies with arterial pulse.^[[2]](#footnote-2)^

### IOP Change from Wake to Sleep States

Relative fluctuations in IOP associated with going from waking state to sleep will be assessed by:

- Pneumotonometer every two hours from 6:00 pm until two IOP measurements have been taken after subject has gone to bed, with the first measurement at least ½ hour after having gone to bed
- Continuously with TF

Change in IOP from wake to sleep as measured by tonometer will be computed by:

1. Averaging IOP of the two tonometer measurements prior to going to sleep
2. Averaging IOP of the two tonometer measurements subsequent to going to sleep

Only subjects with average waking IOP at least 3 mmHg lower than sleep IOP will be included in the analysis. Difference between wake and sleep will be measured by subtracting average of the last two tonometer measures before going to bed from the average of the first two tonometer measurements subsequent to going to bed. Our aim then is to demonstrate a significant increase in TF-measured IOP in those subjects who displayed a meaningful difference on a standard tonometer.

It should be noted that 3 mmHg was chosen as the minimally important difference (MID), based on typical repeatability standard deviations of tonometers that vary between 2.5 mmHg and 4 mmHg^[[3]](#footnote-3)^. Assuming repeatability is about 3.0 mmHg, a change of 3 mmHg has about an 85% chance of reflecting true change in IOP.

### Ocular Pulse

As described in the Section ‎1.2, HR will be recorded three times during the night while TF is installed and recording continuously. Using these data we will relate Ocular Pulse as measured by TF to HR recorded directly.

## Endpoints

### Safety

Adverse events (AE's) including serious AE's (SAE's) occurring at any time during the trial or follow up, whether or not deemed related to study device. Safety measurements will include standard slit-lamp examination.

### Primary Efficacy

This study has the following two, co-primary TF endpoints for each subject:

1. Linear correlation between Time and Continuous TF recordings from approximately 4 hours preceding going to bed to 4 hours after. Relationship between TF and Time will be obtained by modeling the former against the latter using a second order polynomial^[[4]](#footnote-4)^. Linear correlation between TF and Time is the standardized β obtained from the model.
2. Percent difference between frequency of ocular pulsation and HR scored dichotomously:
   - Accurate = "Yes," if
   - Accurate = "No" otherwise

Ocular Pulse will be computed from TF either manually blinded to HR or analytically (e.g. Fast Fourier Transform). Fifteen percent (15%) difference between TF and HR measurements is specified because of the expected events, such as eye and lid movements, which introduce noise to TF measurement.

### Secondary Efficacy

Secondary efficacy endpoints include, for each subject:

- Subject Acceptance of TF, which will be measured on a 5 point analog scale where 5, indicates high acceptance of TF and 1 indicates low acceptance.
- Categorization of subject diurnal rhythm of IOP as measured by TF and assignment to pre-specified diurnal rhythms identified from the literature.

### Performance

- Validity of TF recording at the interval and subject levels scored dichotomously:
  - 0 – invalid
  - 1 – valid

## Analysis Sets

### Safety Analysis Set

The safety analysis set will consist of all patients for whom a recording with TF was initiated.

### Primary Efficacy Analysis Set

The primary efficacy analysis set will consist of all subjects with no major entry violations, as determined by blind review.

Subjects analyzed for Ocular Pulse must have valid data on TF and HR concurrently.

Subjects analyzed for wake/sleep change in IOP must have:

- A least one valid tonometer measure prior to going to bed and one subsequent, and at least 80% valid TF data before going to bed and 80% subsequent to going to bed.
- Difference between average tonometer measurement prior and subsequent to going to bed of 3 mmHg (or single tonometer measurement pre and/or post as available).

Treatment of Missing data:

For both TF and Ocular Pulse only observed data will be used. At the same time, modeling of TF wake/sleep data will be done over the whole wake/sleep period in the presence of up to 20% missing data. In essence this means that missing TF data will be imputed using model fitted to observed subject data.

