### Primary Efficacy

#### Wake/Sleep Correlation

Stage 1: Assessing Validity of Subjects

As noted, only subjects with IOP increases of at least 3 mmHg from wake to sleep, as measured by hand-held tonometer will be included. Thus, Stage 1 of this analysis will consist of evaluating IOP differences between wake and sleep to determine those subjects who will be included in this primary efficacy analysis.

Stage 2: Testing of co-primary endpoint

The following hypotheses will be tested

H_0_: ρ = 0

H_1_: ρ ≠ 0

Where ρ is the correlation between TF and Time over 8 hours, the first four being in a waking state and the subsequent 4, after going to bed.

The relationship between TF and Time over the wake/sleep period will be modeled with the following equation:

TF_i_ = C + B_1_Time_i_ + B_2_Time_i_^2^

Where,

TF_i_ – TF recording at Time i

B_1_ – Weight of linear term (linear slope)

B_2_ – Weight of quadratic term

The statistical hypotheses will be tested by:

- Obtaining for each subject β for the linear term from the model (i.e. the standardized B of the linear term)
- Transforming each β using Fisher-z
- Comparing the mean z-transformed correlation to 0 using a one-sample t-test with two-sided alpha=0.05.

We will conclude success on this primary endpoint if the correlation is significantly greater than 0; i.e. positive and significant.

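### The protocol gives conflicting rules for missing TF data; if fitted values were counted as data, the reported wake/sleep β would be overstated by about 5% at the 20% limit

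*Protocol*

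**What the plan says.** Protocol section 9.6.2 (Primary Efficacy Analysis Set) admits a subject to the wake/sleep analysis with "at least 80% valid TF data before going to bed and 80% subsequent to going to bed". Its paragraph on missing data then makes three statements:

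- The first sets the general rule: "For both TF and Ocular Pulse only observed data will be used".
- The second lets the wake/sleep curve be fitted across all 8 hours even when as much as a fifth of a subject's recordings is absent.
- The third explains how the second is meant: "In essence this means that missing TF data will be imputed using model fitted to observed subject data".

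Section 9.8.4 (Wake/Sleep Correlation) models TF for each subject as a quadratic in Time. The endpoint is the standardized linear coefficient: "Obtaining for each subject β for the linear term from the model". Each β is Fisher-z transformed, and the test is: "Comparing the mean z-transformed correlation to 0 using a one-sample t-test with two-sided alpha=0.05". Success requires a positive and significant mean, with no minimum size of β. Neither section says whether the SDs used to standardize β are taken over the observed points or over a completed series.

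**The concern.** The first and third statements on missing data govern the same TF recordings for the same co-primary endpoint, and they give opposite instructions. An analyst could follow either and claim to have followed the protocol.

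The choice can matter because the endpoint is a standardized coefficient. A value read off the subject's own fitted curve has no residual. Adding such values leaves the raw slope unchanged but reduces the SD of TF, which is in the denominator of β. Under that reading, the more of a recording is missing, the stronger its relation to Time appears. Section 9.8.4 sets no minimum β, so the reported correlation is what a reader will use to judge how well the device tracks the wake/sleep change.

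**Working it through.** **Inputs.** Planning β 0.708 (SD 0.285) and Fisher-z mean 1.073 (SD 0.544), from section 9.7. Missing share up to 20% on each side of bedtime, from section 9.6.2. One TF recording every five minutes, from section 9.2, so 8 × 60 / 5 = 96 points in 8 hours.

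**The plan's own figure.** d = 1.073 / 0.544 = 1.972. A two-sided one-sample t-test at 0.05 with n = 10 (noncentral t) has power 99.98%. The stated power of over 95% reproduces.

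**Effect of filling, by algebra.** Points that lie on the least-squares curve leave B1 unchanged. With a random missing share f, explained variance stays at R² and residual variance falls to (1 − f)(1 − R²). β is therefore multiplied by

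1 / √[R² + (1 − f)(1 − R²)].

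Take R² ≈ 0.708² = 0.501, ignoring the small quadratic part:

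- f = 0.05: 1/√(0.501 + 0.95 × 0.499) = 1/√0.975 = 1.013
- f = 0.10: 1/√(0.501 + 0.90 × 0.499) = 1/√0.950 = 1.026
- f = 0.20: 1/√(0.501 + 0.80 × 0.499) = 1/√0.900 = 1.054, so 0.708 becomes 0.746

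The upper limit at f = 0.20, as R² goes to 0, is 1/√0.80 = 1.118.

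**Effect of filling, by simulation.** 96 points, 9 of 48 (18.75%) missing on each side of bedtime, Time centred at bedtime, true β 0.708. Mean β:

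| Errors | Gaps | Complete | Observed only | Filled |
|---|---|---|---|---|
| Independent | random | 0.709 | 0.710 | 0.741 |
| Independent | blocks | 0.710 | 0.711 | 0.742 |
| Independent | window ends | 0.710 | 0.644 | 0.739 |
| Independent | around bedtime | 0.711 | 0.747 | 0.743 |
| AR(0.8) | random | 0.723 | 0.723 | 0.750 |
| AR(0.8) | blocks | 0.723 | 0.726 | 0.751 |
| AR(0.8) | window ends | 0.725 | 0.662 | 0.727 |
| AR(0.8) | around bedtime | 0.721 | 0.760 | 0.752 |

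A second model, TF = 0.43t − 0.03t² + N(0,1) at 97 points on t from −4 to 4, gives a complete-data β of 0.707. Filling gives 0.739 to 0.745 at 20% missing, depending on the gap pattern, and 0.714 at 5%.

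Two things follow. With independent errors, filling overstates β against complete data in every pattern. The observed-only β also moves, by where the gaps lie: down when the ends are missing (shorter time range) and up when the middle is missing.

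**Effect on the test.** Simulated at n = 10, positive rejections, observed-only against filled:

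| Gaps | True mean z = 0 | True mean z = 0.2 | True mean z = 1.073 |
|---|---|---|---|
| random | 0.0207 / 0.0207 | 0.163 / 0.165 | 1.000 / 1.000 |
| window ends | 0.0287 / 0.0300 | 0.192 / 0.195 | 1.000 / 1.000 |
| around bedtime | 0.0260 / 0.0260 | 0.193 / 0.192 | 1.000 / 1.000 |

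The decision hardly depends on the reading. The reported mean does: with random gaps at the planning value, mean Fisher-z is 1.082 observed-only and 1.156 filled.

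**The case against.** The strongest reply is that the inflation is not in the text. The imputation sentence opens as a gloss on the one before it, the model is described as fitted to observed data, and section 9.8.4 takes β from that model. No section describes restandardizing on a completed series. On this reading the curve simply runs across the gaps and β is unaffected. That reading is available, so a reader who infers that the plan inflates β by construction goes further than the protocol supports. What remains is that the sentence literally prescribes imputation, contradicts its neighbour, and is not neutralized in section 9.8.4.

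Three other strong inferences also fail:

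- **False success.** A reader might infer a threat to type I error or to the co-primary conclusion. Rescaling each subject's β barely moves a t-test against 0, and the simulated rejection rates agree within half a percentage point.
- **Large bias when the window ends are missing.** The contrast of 0.644 observed-only with 0.739 filled looks like heavy inflation. The complete-data value is 0.710, so most of the difference is attenuation of the observed-only β (−0.066). Filling adds 0.029, and only 0.002 under AR(0.8) errors (0.725 to 0.727).
- **Wrong error bars.** Section 9.8.4 specifies a t-test and no confidence interval for β, and the t-test uses the spread actually observed.

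It is also fair to object that 20% is the limit for entering the analysis and not an expected rate. The protocol gives no expected rate, so the range from 5% to 20% is shown.

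**Conclusion.** The contradiction in section 9.6.2 is real and should be resolved, but the consequence is conditional and modest. If filled values enter the standardization, β is overstated against complete data by about 1% at 5% missing and about 5% at 20% missing (0.707 to about 0.74). If they do not, there is no effect. The co-primary decision is essentially the same under both readings. The harm is to the reported size of the main efficacy estimate, and to the freedom left to choose a rule after the TF data have been seen.

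These sizes rest on assumptions that the protocol does not supply: the gap pattern, independent errors, mild curvature, Time centred at bedtime, and a true β near the planning value. A statistical analysis plan that is not shown may already settle the computation, but the protocol's two sentences would still need to be reconciled.

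**What to change.** Delete the imputation sentence in section 9.6.2. State that the quadratic is fitted to observed TF points only and that no fitted value enters any calculation as data.

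Also state how β is standardized in section 9.8.4. Taking both SDs over the observed points is simple, but it makes β depend on where the gaps fall: in the second model at 20% missing, 0.625 with gaps at the ends and 0.745 with gaps around bedtime, against 0.707 complete. A steadier definition is

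β = B1 × SD(Time over the full 8-hour window) / √[variance of the fitted curve over that window + residual variance of the observed points].

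This gave 0.703 to 0.707 in all gap patterns tested, against 0.707 with complete data. If the residual variance uses the observed count minus 1 as divisor, matching the sample variance used for the curve, the formula reduces to the ordinary standardized β when nothing is missing. It does rely on the quadratic holding across the gaps, which the planned model already assumes.

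The cost is two or three sentences, one extra computation step per subject, and a β slightly less favourable than filling would give in subjects with gaps. Design, sample size and test are unchanged.

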### Performance Analysis Set

The performance analysis set will consist of all patients for whom a TF recording was initiated.

## Sample Size Considerations

This study has two co-primary endpoints so that presentation of sample size is based on demonstrating:

- A significant, positive and linear correlation between TF recordings and time during the wake/sleep period.
- Proportion of accurate TF Ocular Pulsation recording relative to HR (TF within ± 15% of HR) is at least 70%; i.e. 70% is an objective performance criterion (OPC) for demonstrating accuracy of Ocular Pulsation

We wish to have at least 90% power to show both of the above, implying 95% power for rejecting each null hypothesis (0.95 * 0.95 = 0.90, conservatively assuming independence of measurements done for testing the two hypotheses).

Previously collected data provide our best estimate for true linear relationship between TF and Time at 0.708 with a standard deviation of 0.285. After Fisher-z transformations of individual correlations we obtain a mean of 1.073 with standard deviation of 0.544. Given these estimates and using a one-sample t-test versus a null of no correlation, a sample size of 10 provides over 95% power to reject the null for this hypothesis.

At this stage we estimate that on 90% of one-minute thirty-second recordings Ocular Pulse as detected by TF will be within ± 15% of HR measured directly. To demonstrate 0.90 ≥ 0.70 with 95% power requires 53 independent observations using two-sided Exact Binomial confidence interval. In this study, each subject will contribute three (3), one-minute TF_Ocular Pulse_/HR relationships. While within-subject TF-HR agreement is not likely to be independent, we assume at this stage that 90 such observations, obtained from 30 subjects, will provide requisite power; i.e. will provide the equivalent of at least 53 independent observations. As described below, confidence interval will be computed using a mixed logistic model (SAS^®^ PROC GLIMMIX) to account for dependencies in the data. Simulations will be used to assess the assumption that 90 observations from 30 subjects provide at least 95% power. If simulations will indicate that more than 30 subjects are needed, this protocol will be amended accordingly before initiation of trial.

As noted, only subjects whose IOP measurements prior to going to bed and after differ by at least 3 mmHg will be analyzed for wake/sleep difference. Thus subjects will be evaluated on IOP change by tonometer and should some display a lower than 3 mmHg difference, additional subjects will be included until 30 valid subjects for testing IOP increase have been obtained. Evaluation of IOP change on tonometer will be done during the trial before (and blind to) opening of TF data. Subjects not included for testing change in IOP will however be included for testing the hypothesis relating to Ocular Pulse.

In conclusion, at this stage we estimate that 30 completed subjects will participate in this trial. This number may increase depending on simulation results and/or evaluation of subject validity for testing change in IOP from before to after going to bed.

## Statistical Analysis

### Overview

Safety, subject disposition and performance will be conducted on the safety analysis set. Primary and secondary efficacy will be conducted on the efficacy analysis set.

The data will be summarized in tables listing the mean, standard deviation median, minimum, maximum and number of subjects for continuous data, or in tables listing count and percentage for categorical data where appropriate. Tables will be presented by study arm and overall. Data listing by subject will be provided.

All statistical analyses will be performed and data appendixes will be created using the SAS^®^ system. The effects of noncompliance, dropouts, and possible covariates such as Age and Gender will be assessed to determine the impact on the general applicability of results from this study.

### Subject Disposition

Subject disposition will be tabulated; the number of enrolled, exposed, prematurely terminated and completed subjects will be summarized.

A list of dropouts will be prepared including reason for discontinuation, and time of discontinuation. In addition, disposition with regard to replacement will be provided.

### Safety

The safety analyses will be descriptive and narrative in nature, with AEs, including serious AEs (SAEs), coded using MedDRA and tabulated by body system, preferred term, group, severity and relation to procedure. Descriptive statistics and shift analysis tables will be provided as appropriate for Ophthalmological examination results.

### Primary Efficacy

#### Wake/Sleep Correlation

Stage 1: Assessing Validity of Subjects

As noted, only subjects with IOP increases of at least 3 mmHg from wake to sleep, as measured by hand-held tonometer will be included. Thus, Stage 1 of this analysis will consist of evaluating IOP differences between wake and sleep to determine those subjects who will be included in this primary efficacy analysis.

Stage 2: Testing of co-primary endpoint

The following hypotheses will be tested

H_0_: ρ = 0

H_1_: ρ ≠ 0

Where ρ is the correlation between TF and Time over 8 hours, the first four being in a waking state and the subsequent 4, after going to bed.

The relationship between TF and Time over the wake/sleep period will be modeled with the following equation:

TF_i_ = C + B_1_Time_i_ + B_2_Time_i_^2^

Where,

TF_i_ – TF recording at Time i

B_1_ – Weight of linear term (linear slope)

B_2_ – Weight of quadratic term

The statistical hypotheses will be tested by:

- Obtaining for each subject β for the linear term from the model (i.e. the standardized B of the linear term)
- Transforming each β using Fisher-z
- Comparing the mean z-transformed correlation to 0 using a one-sample t-test with two-sided alpha=0.05.

We will conclude success on this primary endpoint if the correlation is significantly greater than 0; i.e. positive and significant.

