### Primary efficacy endpoints

This study has the following two, co-primary TF endpoints for each subject:

1. Linear correlation between Time and Continuous TF recordings from approximately 4 hours preceding going to bed to 4 hours after. Relationship between TF recordings and Time will be obtained by modelling the former against the latter using a second order polynomial^[[1]](#footnote-1)^. Linear correlation between TF recordings and Time is the standardized β obtained from the model.
2. Percent difference between frequency of ocular pulsation and HR scored dichotomously.

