I know the requirements for accurate notification of adverse incidents and I pledge to document and notify such events as described in the protocol.

I pledge to retain all trial-related documents and source data as described. I will provide a Curriculum Vitae (CV) before trial start. I agree that the CV may be submitted to the responsible regulatory authorities.

Signature: Date:

__________________________________________________________________________

Print name:

________________________________________

1. study overview – schematic

| **Exam / Visit (day)** | **Baseline visit** | **Day 1** | **Day 2** |
| --- | --- | --- | --- |
| Demographics | X |  |  |
| Medical and surgical history | X |  |  |
| Pregnancy test^[[5]](#footnote-5)^ | X |  |  |
| Automated objective refraction test | X |  |  |
| Slit lamp examination | X | X | X |
| TBUT | X |  |  |
| Corneoscleral profile evaluation | X |  |  |
| Best corrected visual acuity | X | X | X |
| Topography/keratometry | X |  |  |
| Pachymetry | X | X | X |
| Tonometry (Goldmann) | X | X^[[6]](#footnote-6)^ | X |
| Tonometry (pneumatonometer) | X | X^[[7]](#footnote-7)^ | X^[[8]](#footnote-8)^ |
| Heart rate |  | X^[[9]](#footnote-9)^ | X^8^ |
| SENSIMED Triggerfish® placing |  | X |  |
| SENSIMED Triggerfish® removal |  |  | X |
| Sleep quality assessment |  |  | X |
| Visual analogue scale |  |  | X |
| Patient diary |  | Throughout IOP fluctuation recording; collection on Day 2 | |
| Concomitant medication | On an ongoing basis | | |
| Adverse events / complaints | On an ongoing basis | | |

1. After rising from wake to sleep state IOP flattens out, so that a quadratic term is appropriately fit to the data. [↑](#footnote-ref-1)
2. Krakau CE. Calculation of the pulsatile ocular blood flow. Invest Ophthalmol Vis Sci 1992; 33: 2754-6. [↑](#footnote-ref-2)
3. Kotecha, A. et al. Intraocular pressure measurement precision with the goldmann applanation dynamic contour, and ocular response analyzer tonometers. Ophthomology 2010, in Press. [↑](#footnote-ref-3)
4. After rising from wake to sleep state IOP flattens out, so that a quadratic term is appropriately fit to the data. [↑](#footnote-ref-4)
5. For women of childbearing potential [↑](#footnote-ref-5)
6. 1^st^ eye randomised prior to SENSIMED Triggerfish installation. [↑](#footnote-ref-6)

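### The first co-primary endpoint calls the standardised linear coefficient of a quadratic model a correlation; its value depends on where Time = 0 lies, can exceed 1, and then has no Fisher-z

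*Protocol*

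**What the plan says.** Protocol 5.2.2 states "Linear correlation between TF recordings and Time is the standardized β obtained from the model", and 9.5.2 repeats the definition: "Linear correlation between TF and Time is the standardized β obtained from the model". Section 9.8.4 gives the model as TF = C + B1·Time + B2·Time², in raw powers of Time, and sets three steps: "Obtaining for each subject β for the linear term from the model (i.e. the standardized B of the linear term"; then "Transforming each β using Fisher-z"; then "Comparing the mean z-transformed correlation to 0 using a one-sample t-test with two-sided alpha=0.05". Success requires the result to be positive and significant.

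The hypothesis in 9.8.4 concerns ρ, defined thus: "Where ρ is the correlation between TF and Time over 8 hours, the first four being in a waking state and the subsequent 4". The reason for the quadratic term is given in footnotes 1 and 4: "After rising from wake to sleep state IOP flattens out, so that a quadratic term is appropriately fit to the data".

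The protocol gives no origin or centring for Time, no orthogonal parameterisation, and no rule for |β| ≥ 1.

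**The concern.** The standardised coefficient equals the Pearson correlation when Time is the only regressor. Adding Time² breaks that equality. B1 becomes the tangent slope of the fitted parabola at Time = 0, so it describes one arbitrary point on the curve and not the trend over the 8 hours. Its standardised form has no upper limit of 1, and Fisher-z, atanh(β), does not exist for |β| ≥ 1.

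This is one of two co-primary endpoints, and 9.7 plans to show both. If β depends on an unstated coding choice, so does the outcome of the trial. Where β is undefined, someone must decide after seeing the data whether to drop or truncate those subjects, and dropping them can remove the strongest responders. The planning figures in 9.7 would also describe a different quantity from the one tested.

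**Working it through.** **The plan's own figure.** From 9.7: Fisher-z mean 1.073, SD 0.544, one-sample t-test; two-sided α = 0.05 from 9.8.4. Effect size = 1.073/0.544 = 1.972. At n = 10 the noncentrality is 1.972 × √10 = 6.24 and the power is 0.9998. The stated power of over 95% reproduces (n = 6 already gives 0.967). The fault is in the endpoint definition, not in the power arithmetic.

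**Algebra.** Let Time be recoded as u = t + s. Substituting t = u − s in C + B1·t + B2·t² gives a new linear coefficient B1 − 2·s·B2. SD(Time), SD(TF) and the fitted curve do not change. So β = B1·SD(Time)/SD(TF) moves with s unless B2 = 0.

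**One curve by hand.** Assume a rise that flattens at +4 h: TF = 1 − ((4 − t)/8)², with t in hours from bedtime. Expanded, B1 = 1/8 = 0.125 and B2 = −1/64 = −0.015625. Over −4 to +4 h, SD(t) ≈ 2.309 and SD(TF) ≈ 0.298, a ratio of about 7.746.
- Zero at bedtime (s = 0): 0.125 × 7.746 = 0.968, equal to Pearson r.
- Zero at window start (s = 4): (0.125 + 0.125) × 7.746 = 1.937.
- Zero at window end (s = −4): (0.125 − 0.125) × 7.746 = 0.
- Clock hours 19–27, bedtime 23:00 (s = 23): (0.125 + 0.71875) × 7.746 = 6.536.

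**Three noise-free curves**, 96 points at the 5-minute spacing of 9.2; entries are β:

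| Assumed curve | Pearson r | 0 at bedtime | 0 at window start | 0 at window end | Clock hours |
|---|---|---|---|---|---|
| Rise flattening at +4 h | 0.968 | 0.968 | 1.937 | 0.000 | 6.536 |
| Rise peaking at +2 h | 0.889 | 0.889 | 2.666 | −0.889 | 11.107 |
| Symmetric hump, no trend | 0 | 0 | 3.874 | −3.874 | 22.274 |

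No value above 1 in absolute size has a Fisher-z. The second row changes sign on identical data.

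**With noise.** 97 bursts over 8 h, independent noise set so that Pearson r is about 0.71, 2,000 profiles per shape. For Time counted 0–8 h, corr(Time, Time²) = 0.97.
- Rise −4 to +1 h, then flat: mean β 1.57 with 99% undefined (window start); 0.71 with 0% undefined (bedtime); −0.14 (window end).
- Rise −2 to +1 h, then flat: 1.10 with 66% undefined (window start).
- Rise 0 to +2 h, then flat: −0.12 (window start); 0.71 (bedtime); 1.55 (window end).
- Symmetric rise −2 to +2 h: 14–15% undefined (window start), 0% at bedtime. At 15%, the chance that at least one of 30 subjects is undefined under the 0–8 h coding is 1 − 0.85³⁰ = 0.992.

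**Effect on the test.** A second simulation used 30 subjects, 100 trials, linear effect 0.8 and curvature −0.5 per 4-hour unit, and autocorrelated noise. Fisher-z was undefined in 0% of subjects with zero at bedtime, 72% with zero at window start and 93% on clock hours. With undefined subjects dropped, the trial succeeded in 100%, 47% and 0% of runs respectively.

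**Missing data.** Section 9.6.2 allows up to 20% missing TF data before and after bedtime. For the first noise-free curve, block gaps of just under 20% on each side move β from 0.968 to between 0.892 and 1.083, even with zero at bedtime.

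**The case against.** The window is built around going to bed, so a programmer might well code Time from bedtime. In a complete, symmetric, evenly spaced window β then equals Pearson r, and across six simulated shapes at r near 0.71 no subject was undefined, even with 20% of points missing at random. The earlier data in 9.7 could be Fisher-transformed, so those values were presumably all below 1, which suggests centred coding or plain correlations. Time coding is often left to the SAP. A rise that flattens does not always push β above 1: if it starts only at bedtime, the 0–8 h coding gives −0.12, which is a wrong sign and not an undefined value. Curves antisymmetric about bedtime, having no quadratic component, have an expected β that does not depend on the origin.

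These points limit when the failure occurs; they do not remove it. Bedtime coding is stated nowhere, and the wording of the hypothesis, 8 hours with the first four awake, fits a 0–8 h count at least as well. The window is only approximately symmetric, and block gaps can push even bedtime-centred β past 1, though that example starts from r = 0.968, well above the planning value of 0.708. Nor is this a detail left to the SAP: the protocol itself equates β with the correlation in three places, and a SAP using Pearson r would contradict it.

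**Conclusion.** The concern holds and must be fixed. As written, the first co-primary endpoint is not the correlation named in its hypothesis. Its size and sign depend on an unstated time origin whenever B2 is not 0, and Fisher-z fails for |β| ≥ 1. That much is algebra.

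How often it fails depends on assumed curve shapes, noise and coding, none of which comes from the protocol. Under a 0–8 h coding, Fisher-z was undefined in anything from none to 99% of subjects by shape; where none was undefined (rise from 0 to +2 h), β had the wrong sign. With zero at bedtime and no block gaps the problem disappears. The planned sample size is not shown to be wrong: n = 10 gives 0.9998 power if the planning values are true correlations, and 30 subjects are planned for this test.

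**What to change.** In 5.2.2, 9.5.2 and 9.8.4:
- Define Time as hours from going to bed, −4 to +4.
- Define each subject's correlation as the Pearson correlation of observed TF values with Time, and apply Fisher-z to that. It stays within ±1, does not depend on the origin, and matches ρ in the hypothesis.
- Keep the quadratic model only to describe the shape of the curve, and align the sentence in 9.6.2 on filling gaps from the fitted model.
- Confirm in 9.7 that 0.708 and the Fisher-z values were computed as Pearson correlations.

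If the sponsor prefers to keep the quadratic in the endpoint, orthogonal polynomials built on each subject's own observed times give the same linear value. Centring at bedtime alone is not enough when there are gaps.

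The cost is protocol and SAP wording, with no new data. If the planning values are Pearson correlations, the stated power is unaffected.
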